### Withdrawal and drop-out criteria

The participants had the option to discontinue the study at any time or to exacerbate any serious adverse events. The subjects will be included in the analysis after completing the follow-up.

### Recruitment

Participants will be recruited from the Department of Spine Surgery, Manipal Comprehensive Spine Care Center, Manipal Hospitals Bangalore, on the basis of inclusion and exclusion criteria. The eligible and interested subjects attended a baseline assessment before the surgery, and informed consent was obtained from the subjects by the investigator.

### Assignment of interventions: allocation

The participants will be randomly allocated into the experimental and control groups using block randomization. Fourteen blocks of block size 10 will be used, and the allocation ratio is 1:1. Concealed allocation will be performed with nontransparent envelopes, which will in turn be signed by the respective supervisor, who is uninvolved in subject recruitment. Once the participant reports, one neutral arbitrator will pick an envelope and provide an intervention to the treating therapist. The study flow is demonstrated in (Fig. 1).

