## Methods

### Trial design

This is an assessor-blinded, randomized controlled trial with an interventional and control group.

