### Sample size

The sample size was calculated using G*Power 3 and based on the Oswestry Disability Index standard deviation and effect size reported by Haoming Wang [26] et al. Study power is considered to obtain a *p*-value of less than 0.05. The power of the study is 0.80. Dropout will be considered up to 15% and calculated using the formula “n/1-dropout rate percentage”. The total number of participants in the study, including dropouts, is 136.

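### A single, published block size of 10 at one centre makes some assignments predictable, and the envelope rule states no order of use

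*Protocol article*

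**What the plan says.** The section on allocation in the Protocol article sets the scheme: "Fourteen blocks of block size 10 will be used, and the allocation ratio is 1:1". It then describes the safeguards: "Concealed allocation will be performed with nontransparent envelopes, which will in turn be signed by the respective supervisor, who is uninvolved in subject recruitment". The moment of allocation is described as follows: "Once the participant reports, one neutral arbitrator will pick an envelope and provide an intervention to the treating therapist".

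Other sections give the setting:

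- Recruitment names one source of patients: "Participants will be recruited from the Department of Spine Surgery, Manipal Comprehensive Spine Care Center, Manipal Hospitals Bangalore". It also says that "informed consent was obtained from the subjects by the investigator".
- Trial design states the blinding: "This is an assessor-blinded, randomized controlled trial with an interventional and control group". No blinding of patients or therapists is stated.
- Sample size gives the total: "The total number of participants in the study, including dropouts, is 136".
- Eligibility criteria include exclusions that can only be judged after surgery and that leave room for discretion, such as poor general health after the operation and new or worsening symptoms.
- Trial status puts the start of recruitment at 15 December 2024 and estimated completion at 14 April 2027.

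**The concern.** When every block holds exactly five of each arm and the size is public, the end of a block can be worked out from its beginning. Opaque envelopes stop someone reading the next assignment, but not inferring it from past ones. Here past assignments could be observed on site. The two programmes differ visibly (coping skills, relaxation and family education in one, standard exercise in the other), therapists know the arm, and all patients come through one department.

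Foreknowledge matters because consent is obtained by the investigator and some exclusions involve judgement after surgery. Someone who expects a particular arm next could let that affect who is included or when a participant reports for allocation. Selection of this kind happens before any outcome is measured, so assessor blinding does not prevent it and the analysis cannot reliably undo it. One of the two primary outcomes, pain on the visual analogue scale, is described as self-reported, which further limits what assessor blinding protects.

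The second weakness is the verb *pick*. The text does not say that envelopes are taken in the generated order. If they were drawn freely from a pile, the list of fourteen balanced blocks would not be the sequence actually applied.

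**Working it through.** **Inputs.** Block size 10, 14 blocks, ratio 1:1 (section on allocation); total 136 (Sample size). Assumptions not in the article: envelopes are used in block order, and the observer knows the block size, where each block starts and all earlier assignments in the block.

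**The plan's own figure.** 136 / 10 = 13.6, rounded up to 14 blocks, or 14 × 10 = 140 slots. The block count agrees with the total. The 136 itself cannot be rebuilt, because the effect size and SD are not given. The dropout step is consistent with 115 completers: 115 / (1 − 0.15) = 135.3, rounded up to 136.

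**Assignments known with certainty.** An assignment is certain once one arm has used its five slots. After k assignments in a block, the probability of this is 2 × C(5, k − 5) / C(10, k):

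| Position in block | Calculation | Probability that it is certain |
|---|---|---|
| 1 to 5 | – | 0 |
| 6 | 2 / 252 | 0.008 |
| 7 | 10 / 210 | 0.048 |
| 8 | 20 / 120 | 0.167 |
| 9 | 20 / 45 | 0.444 |
| 10 | 10 / 10 | 1.000 |
| **Sum** | | **1.667** |

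The closed form agrees: with m = 5 per arm, 2m / (m + 1) = 10 / 6 = 1.67 per block, or 16.7%. The other 83.3% are still undetermined when made.

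The 136 participants fill 13 blocks and six places of the fourteenth: 13 × 1.667 + 0.008 = 21.7, about 22. If all 140 slots were used: 14 × 1.667 = 23.3.

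**Best guess.** Always guess the arm with more slots left. Expected correct guesses per block = m + 2^(2m − 1) / C(2m, m) − 1/2 = 5 + 512 / 252 − 0.5 = 6.53, or 65.3%, against 5 by chance. For 136 participants, the six places of the last block contribute 0.500 + 0.556 + 0.556 + 0.595 + 0.595 + 0.643 = 3.44. The total is 13 × 6.532 + 3.44 = 88.4, and 88.4 / 136 = 65.0%.

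**Would varied block sizes help?** Simulated sequences of 136, guessing the arm that is behind in the running count:

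| Block sizes | Correct guesses |
|---|---|
| Fixed 10 | 65.0% |
| Mixed 8, 10, 12 | 65.0% |
| Mixed 6, 8, 10 | 66.3% |
| Mixed 4, 6, 8 | 68.0% |

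Varying and withholding the sizes takes away certainty, because the observer no longer knows where a block ends. It does not lower the guessing rate, and small blocks raise it.

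**Order of use.** The figures above apply only if envelopes are taken in block order. If they are drawn freely from the whole stack, the countdown does not apply, but the planned blocked sequence is not followed either. The two weaknesses are alternatives and do not add up.

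**The case against.** The article states real safeguards: nontransparent envelopes, a signature by a supervisor outside recruitment, and a neutral arbitrator. A reader might infer from the fixed blocks that concealment fails altogether. The text does not support that. Nothing says that the investigator who obtains consent learns earlier assignments; only the therapist is said to be told. This objection stands, and it makes the figures upper bounds.

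Three other strong readings also go too far:

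- *The arbitrator can choose the arm.* Free picking among opaque envelopes does not reveal their contents. Choosing would need opened or marked envelopes, which nothing suggests.
- *The centre is unblinded.* The trial is assessor-blinded. What can be said is that no blinding of patients or therapists is stated.
- *An assessor who learns one arm can infer the others in the block.* In a 5:5 block, knowing one arm moves the chance that another given patient is in the opposite arm only from 1/2 to 5/9 (56%).

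It is also fair that numbering and sealing of envelopes are details an article may leave to the full protocol, so their absence is not a fault. The single block size is different: the article states it and makes it public. The envelope rule is likewise criticised for the wording it uses, which should not be open to a reading that undoes the blocking.

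**Conclusion.** The point holds in a limited form. One fixed, disclosed block size at a single centre with therapists aware of the arm leaves allocation partly predictable. At most about 22 of 136 assignments (16%) could be known with certainty, and about 65% guessed correctly. Both figures assume use in block order and full knowledge of earlier assignments and block starts. That knowledge is plausible in one department but is not stated. With less knowledge, the figures fall towards none certain and 50% guessed. Concealment is weakened and incompletely assured; it is not shown to fail, and there is no evidence that selection has occurred. The change is a cheap improvement worth making while recruitment continues.

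**What to change.** For the remaining participants:

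1. Generate a new 1:1 list with randomly varied block sizes that are not small, for example 8, 10 and 12. Withhold the sizes from recruiting, treating and assessing staff, and do not publish them while the trial is recruiting.
2. Replace the wording about picking an envelope with: the arbitrator opens the next envelope in the fixed sequence, only after consent, the baseline assessment and final eligibility, including the postoperative exclusions, have been recorded.

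The gain is that nearly all assignments known with certainty disappear and the order of use becomes unambiguous. The amendment should not claim that guessing becomes harder: the best-guess rate stays near 65%.

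The cost is a short amendment, a new list and relabelled envelopes, with no extra patients or staff. The possible imbalance at the end is slightly larger. Stopping at 136 under the present scheme leaves six places used in the last block, so at worst 5 against 1, a difference of 4. A last block of 12 stopped halfway could leave 6 against 0, a difference of 6. If the present list is abandoned mid-block, that block can add a difference of up to 5.

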**Fig. 1 Fig1:**
[figure not shown]
Flow of the study

### Interventions

The patients were allocated to the interventional arm or the control arm. The control group interventions focused on treating the physiological and anatomical causes of the patient’s illness. Both groups will receive supervised treatment in IPD (two sessions), supervised treatment in OPD (six sessions), and unsupervised treatment from 4 to 12 weeks. Each session will last for approximately 40 to 45 min. Patients are instructed to perform the home exercises daily, and a self-reported diary will be used to evaluate patient compliance with the exercises and instructions.

### Biopsychosocial model of rehabilitation

The intervention group will participate in a rehabilitation program based on the biopsychosocial model of rehabilitation. The rehabilitation protocol is focused on the biological, psychological, and sociological factors influencing patients’ illnesses. This goal can be attained by treating physical symptoms, managing thoughts and cognitive processes, exercising, and providing family education. The biopsychosocial model of rehabilitation (Appendix: I) will include pain coping skill training, progressive muscle relaxation, pleasant activity, and education of family members along with exercise. The pain coping skill training and progressive muscle relaxation begin on first session which is postoperative day (POD) and advise patients to practice it when they experience an increase in pain. Components of biopsychosocial factors and exercise will be given throughout the sessions. On POD-1, the subjects will be instructed to use mini-practices during the day, and the education of family members will be provided. The participants will learn to identify and substitute automatic negative thoughts with constructive thoughts during the breach exercise and during the rest of the day. In later sessions, they learn how to alternate activities and rest, as well as how to manage negative thoughts. The participants are instructed to imagine calming pictures, such as the sea or the mountains, and to perform leisure activities such as reading. Each session will incorporate coping skills, which will be integrated into functional activities throughout the day [15, 18, 19]. As the final supervised session progresses, the biopsychosocial rehabilitation model will be addressed by the therapist in all of its parts. All the sessions except POD-1 ended with home advice and a demonstration of the home exercise program.

### Rehabilitation for the control group

The control group rehabilitation interventions (Appendix: II) will focus on treating the physiological and anatomical causes of the patient’s illness, including range of motion exercises, strengthening exercises, and advice for returning to normal activities. The rehabilitation begins with patient education and breathing exercises on POD-1. During POD-2 muscle activation exercise, range of motion exercises for the lower limb and walking with support are performed. The following sessions will consist of returning to normal activity advice, activating and strengthening exercises of muscles, and a demonstration of home exercises. Training intensity progression will be done on the basis of patients’ self-perception of pain.

### Outcomes

Baseline assessments will be performed before surgery using the Oswestry Disability Index, visual analog scale, Timed Up and Go test, Pain Catastrophizing Scale, and SF-36 questionnaire. The participants will be reexamined at 2, 4, and 12 weeks after surgery.

#### Primary outcomes

• Oswestry disability indexIt is presented as a score of 0–100, where the lowest score represents the minimal level of low back pain disability. The ODI has good test‒retest reliability, validity, and internal consistency in chronic back pain and spine surgery populations. The ODI has excellent telephonic reliability and validity (with a correlation coefficient of 0.98 and a range of 0.95–1). The minimum clinically important difference (MCID) has been reported to be between 4 and 10.5 points and is clinically significant [20].• Visual analog scale (VAS)The VAS is a self-reported outcome measure used to assess the level of pain that a patient experiences. Pain is measured on an 11-point scale where 0 is considered no pain and 10 is the worst pain. The visual analog scale is a reliable and valid tool for measuring pain, with a minimum clinically important difference (MCID) of 1.4 cm (14% of the total length of the scale), which is clinically significant [21].

#### Secondary outcomes

• Timed Up and Go test (TUG)In the Timed Up and Go test, the patient should get up from the chair, walk a distance of 3 m twice, and sit down as quickly as possible. A minimum clinically important difference (MCID) of 3.4 s was established, which is clinically significant [22].• Pain catastrophizing scale (PCS)The PCS is a self-report questionnaire that measures an individual’s tendency to catastrophize pain. The PCS total scores range from 0 to 52. The PCS, as a full scale, is concluded to be a reliable measure with high test‒retest reliability [23].• SF-36v2The SF-36v2 is a self-reported outcome measure. It consists of 36 questions and 8 subscales investigating physical function, pain, vitality, role Limitations, social functioning, mental Health, emotional problems, and general Health status. The scale is scored from 0 to 100, with 0 representing the lowest quality of Life and 100representing the highest quality of life [24, 25]. The questionnaire will be used for baseline assessment and final follow-up (Fig. 2).

**Fig. 2 Fig2:**
[figure not shown]
Time plan of the study

### Sample size

The sample size was calculated using G*Power 3 and based on the Oswestry Disability Index standard deviation and effect size reported by Haoming Wang [26] et al. Study power is considered to obtain a *p*-value of less than 0.05. The power of the study is 0.80. Dropout will be considered up to 15% and calculated using the formula “n/1-dropout rate percentage”. The total number of participants in the study, including dropouts, is 136.

### Data analysis

The analysis of clinical outcomes will be performed using JAMOVI version 2.3.28. The normality of the data will be evaluated using the Shapiro‒Wilk test and analysis of variance with repeated measures or general linear models for intergroup differences. Only subjects completing all follow-ups will be included in the analysis.

The detailed analysis of the study results will provide valuable information on the significant influence of the biopsychosocial rehabilitation model on the overall functional disability, pain, and quality of life of patients who have undergone lumbar fusion surgery. Intention-to-treat analysis will be used to handle the missing values of participants who drop out from the study due to unavoidable reasons. MCMR test will be done, and “expectation maximization” test will be applied if the data is missing in random.

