**Methods:**

An assessor-blinded randomized controlled trial will recruit 136 participants, and randomly allocate the participants into two groups. The intervention group will follow the biopsychosocial rehabilitation model, whereas the control group will be subjected to a routine standard protocol. Assessments will be done at baseline, 2, 4, and 12 weeks post-surgery. The normality of the data will be evaluated using the Shapiro‒Wilk test and analysis of variance with repeated measures or General linear models for intergroup differences. This protocol follows all required ethical guidelines.

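### The analysis sentence offers two non-equivalent methods without baseline adjustment, and permits a test that averages the pre-surgery score into the treatment comparison

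*Protocol article*

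**What the plan says.** The Data analysis section of the Protocol article names a Shapiro-Wilk check of normality and "analysis of variance with repeated measures or general linear models for intergroup differences". It does not say which of the two methods applies, which visits form the repeated factor, whether the tested effect is the group main effect or group-by-time, or whether the baseline score is a covariate.

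The schedule is clear. Under Outcomes, "Baseline assessments will be performed before surgery", and then "The participants will be reexamined at 2, 4, and 12 weeks after surgery". The abstract lists the same four occasions together: "Assessments will be done at baseline, 2, 4, and 12 weeks post-surgery". For SF-36, the Secondary outcomes section restricts collection: "The questionnaire will be used for baseline assessment and final follow-up". I take that specific statement as governing SF-36.

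The Sample size section rests on a p-"value of less than 0.05" and states "The power of the study is 0.80". The calculation is "based on the Oswestry Disability Index standard deviation and effect size reported by" a cited study; neither figure is printed.

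**The concern.** Baseline precedes surgery and all study treatment, so randomisation makes the expected arm difference there zero. If baseline is a level of the repeated factor, the group main effect averages that zero with the post-surgery differences. It then estimates something smaller than the treatment effect. The phrase about intergroup differences makes this between-group test an easy one to reach for.

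The group-by-time interaction avoids the dilution. With four visits, however, it asks only whether the two profiles differ in any way. It has three degrees of freedom and gives no single difference to report for ODI or pain.

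A general linear model could be an ANCOVA on baseline, which avoids both problems, but the text does not say so. The sentence therefore covers tests that estimate different quantities with quite different power, and does not choose among them in advance. Both named methods rest on normal errors, so the Shapiro-Wilk result gives no basis for choosing between them.

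**Working it through.** **Inputs from the Protocol article:** N = 136 including 15% dropout, 1:1 allocation, alpha 0.05, power 0.80, visits at baseline and 2, 4 and 12 weeks, SF-36 at two occasions.

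**Assumptions not in the document:** two-sided test, compound symmetry with equal variances, within-patient correlation ρ = 0.3, 0.5 or 0.7, and standardised effect d.

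**1. The plan's own figure.** With no effect size or SD printed, 136 cannot be reproduced forwards. Backwards, 115/0.85 = 135.3, which rounds up to 136; 116/0.85 = 136.5. That fits 57 to 58 evaluable patients per arm. A two-sided t-test with 80% power then implies d = 0.529 (57 per arm) or 0.525 (58 per arm). I use d = 0.526 and n = 58 per arm, where an unadjusted single-visit t-test has power 0.80.

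**2. Dilution.**
- Constant post-surgery effect, four visits: (0 + d + d + d)/4 = 0.75d.
- SF-36, two visits: (0 + d)/2 = 0.50d.

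**3. Power, four visits, constant effect.**
- Main effect: standardised effect 0.75d/√((1+3ρ)/4) = 0.3945/√(0.475, 0.625, 0.775) = 0.572, 0.499, 0.448.
- Group-by-time: noncentral F on 3 and 3(2n−2) = 342 df. The squared deviations sum to 0.75d², so λ = (n/2)(0.75d²)/(1−ρ) = 6.018/(1−ρ) = 8.60, 12.04, 20.06.
- Mean of the three post-surgery visits adjusted for baseline: d/√((1+2ρ)/3 − ρ²) = 0.526/√(0.443, 0.417, 0.310) = 0.790, 0.815, 0.945.

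| Test | ρ = 0.3 | ρ = 0.5 | ρ = 0.7 |
|---|---|---|---|
| Group main effect, baseline as a level | 0.86 | 0.76 | 0.67 |
| Group-by-time, 3 df | 0.68 | 0.84 | 0.97 |
| Post-surgery visits only, unadjusted | 0.97 | 0.93 | 0.88 |
| Post-surgery mean, baseline-adjusted | 0.99 | 0.99 | >0.99 |
| Week 12 alone, ANCOVA | 0.84 | 0.90 | 0.98 |

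**4. Two visits, as for SF-36, at the same assumed d.**
- Main effect: 0.263/√((1+ρ)/2) = 0.326, 0.304, 0.285; power 0.41, 0.37, 0.33.
- Group-by-time, which here is the change-score test on 1 df: d/√(2(1−ρ)); power 0.66, 0.80, 0.95.
- ANCOVA: d/√(1−ρ²) = 0.551, 0.607, 0.737; power 0.84, 0.90, 0.98.

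**5. Sensitivity to the shape of the effect.**
- Growing in equal steps per visit to d at week 12 (0, d/3, 2d/3, d), the main effect recovers 50%.
- Growing in proportion to weeks (0, d/6, d/3, d), it recovers 37.5%.

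| Test (ρ = 0.3/0.5/0.7) | Equal steps per visit | In proportion to weeks |
|---|---|---|
| Main effect | 0.53/0.43/0.36 | 0.33/0.27/0.22 |
| Group-by-time | 0.54/0.70/0.91 | 0.56/0.72/0.92 |
| Adjusted post-surgery mean | 0.80/0.83/0.92 | 0.56/0.59/0.71 |
| Week-12 ANCOVA | 0.84/0.90/0.98 | 0.84/0.90/0.98 |

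**The case against.** The strongest reply is that the document never commits the error. It does not state that baseline is a level of the repeated factor or that the main effect is the test. A repeated-measures ANOVA of weeks 2, 4 and 12 fits the wording, and so does an ANCOVA under the general linear model label. A reader might infer that the plan counts baseline as an outcome and rejects adjustment; the text supports only that it permits this. The exception is SF-36: with one post-surgery score, a repeated-measures ANOVA cannot be run without baseline. SF-36 is secondary, however.

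A second reply is that covariates and contrasts are commonly left to a fuller plan, which is not shown. That holds for the covariance structure and similar detail. It does not remove the point: the article itself names the analysis, and names it as two alternatives with different targets.

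Third, baseline adjustment does not win every comparison. With a constant effect at ρ = 0.3, the diluted main effect (0.86) slightly exceeds a week-12 ANCOVA (0.84), because it averages three treated visits. At ρ = 0.7 the interaction (0.97) is close to both adjusted analyses. If the effect grows in proportion to weeks, the interaction beats the adjusted post-surgery mean at ρ = 0.5 and 0.7. A claim that the plan always loses power to ANCOVA is not supported.

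Finally, a reader might infer that the Shapiro-Wilk result selects the model. The sentence joins the test and the models by a plain conjunction and does not say so.

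**Conclusion.** The point holds in conditional form. The sentence joins two non-equivalent analyses, names no baseline adjustment, and permits a main-effect test that keeps 75% of a constant post-surgery effect. For SF-36 its repeated-measures option must include baseline, and the main effect there keeps 50%.

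The dilution fractions follow from the visit schedule and the assumed effect shape. The power figures also depend on d, ρ and compound symmetry, none of which the document gives. With a constant effect, the diluted main effect gives up about 0.12 to 0.33 of power against the baseline-adjusted post-surgery mean (0.988 − 0.864 at ρ = 0.3; 0.999 − 0.668 at ρ = 0.7). For SF-36 the loss against ANCOVA is about 0.42 to 0.64 (0.838 − 0.414; 0.976 − 0.331). Against a group-by-time test the gain is small when ρ is high. For the four-visit outcomes, the firmer objection to that test is that it yields no single effect estimate.

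This should be corrected before analysis. It does not show that the trial will be analysed wrongly.

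**What to change.** Replace the sentence with one prespecified model for ODI and VAS, and likewise for TUG and PCS:

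- Outcomes: the 2-, 4- and 12-week scores only.
- Fixed terms: arm, visit, arm-by-visit and the baseline score as covariate.
- Primary result: one arm contrast named in advance, either the difference at a stated visit or the average over the three visits, with its 95% confidence interval. The sensitivity results show that this choice matters, so it should follow from when the benefit is expected.
- SF-36: ANCOVA of the final score on the baseline score.
- Normality: examine model residuals, and state that the Shapiro-Wilk result does not choose the model.

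Adjustment for one versus two fused levels is optional and not part of this point.

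The cost is a wording amendment. All scores needed are already scheduled, and no visit, measurement or patient is added. The article reports recruitment as ongoing with completion estimated for April 2027, so the model can still be fixed before the final data are analysed.

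### The plan orders both a completers-only and an intention-to-treat analysis and labels neither as primary; the completers-only rule can bias the randomised comparison

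*Protocol article*

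**What the plan says.** The Data analysis section of the protocol article sets two rules.

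- Its first paragraph closes with "Only subjects completing all follow-ups will be included in the analysis".
- Its second paragraph says "Intention-to-treat analysis will be used to handle the missing values of participants who drop out from the study due to unavoidable reasons". It then adds a test of the missingness mechanism, and says of expectation maximization that this "test will be applied if the data is missing in random".

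The Withdrawal and drop-out criteria section has a related condition: "The subjects will be included in the analysis after completing the follow-up". It does not say that every visit is needed; only the Data analysis section does. The same section says "The participants had the option to discontinue the study at any time".

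On the visits themselves, the Outcomes section says "The participants will be reexamined at 2, 4, and 12 weeks after surgery". The Sample size section allows for dropout of up to 15% and says "The total number of participants in the study, including dropouts, is 136".

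None of these statements calls its rule primary, per-protocol or sensitivity, and none ties it to a particular outcome.

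**The concern.** If only patients with every follow-up are analysed, those who dropped out have no place in the data set, and their missing values need no handling. If intention-to-treat with expectation maximization is followed, patients with incomplete follow-up are analysed and the completers rule is broken. An analyst can obey one sentence only by breaching the other. Because neither is named as primary, the choice could be made after results are known.

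The completers rule is also a poor choice in itself. It selects patients on something that happens after randomisation, so the groups compared are no longer the groups randomised. It discards usable data too: a patient with a valid 12-week ODI who missed week 2 is dropped. The intention-to-treat sentence has a milder form of the same weakness. It covers only dropouts whose reason was unavoidable, a term the article does not define, so inclusion turns on a judgement made after allocation.

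This is not detail left to a statistical analysis plan. The article fixes the analysis set itself, in two incompatible ways.

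**Working it through.** **1. The two rules side by side**

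| Patient | Completers rule | Intention-to-treat sentence |
|---|---|---|
| Seen at weeks 2, 4 and 12 | in | in |
| Seen at weeks 4 and 12, missed week 2 | out | not addressed unless counted as a dropout |
| Dropped out, reason judged unavoidable | out | in, values estimated |
| Dropped out, other reason | out | not covered |

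The rules give opposite answers in the third row. In the second and fourth rows, the completers rule excludes patients whom the other sentence leaves unresolved.

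**2. How many patients are affected**

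Inputs from the Sample size section: 136 in total, dropout up to 15%, inflation by n/(1 - dropout). The ODI effect size and SD are not given as numbers, so the underlying n cannot be reproduced. Only the dropout step can be checked:

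- 57 per arm / 0.85 = 67.06, rounded up to 68 per arm, which is 136 in total.
- 116 in total / 0.85 = 136.5, also close to 136.

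The stated total therefore fits about 57 to 58 evaluable patients per arm. At the planned dropout:

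- Completers: 136 x 0.85 = 115.6, about 116.
- Randomised but excluded: 136 x 0.15 = 20.4, about 20.

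**3. What the exclusion could do to the comparison (illustration)**

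Let p be the share lost in an arm and g the mean outcome of lost patients minus that of completers. The mean of everyone in the arm is the completer mean + p x g, so the completer mean is off by -p x g. The error in the difference between arms is -(pT x gT - pC x gC), where T is intervention and C is control.

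Assumptions, none of them in the document: 15% lost per arm; lost patients 10 ODI points worse in one arm only; 58 analysed per arm; SD 12 to 18; no true effect; normal approximation at two-sided 5%.

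- Shift = 0.15 x 10 = 1.5 ODI points.
- SE = SD x sqrt(2/58).

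| SD | SE | Shift / SE | Type I error |
|---|---|---|---|
| 12 | 2.23 | 0.67 | 10.3% |
| 15 | 2.79 | 0.54 | 8.4% |
| 18 | 3.34 | 0.45 | 7.3% |

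Other assumed cases, in SD units with 68 randomised per arm:

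| Loss, intervention / control | Lost patients worse by | Shift | Type I error |
|---|---|---|---|
| 15% / 15% | 0.5 SD in both arms | 0 | 5.0% |
| 20% / 10% | 0.5 SD in both arms | 0.05 SD | 5.8% |
| 15% / 15% | 0.5 SD, intervention only | 0.075 SD | 6.9% |
| 20% / 10% | 0.5 SD, intervention only | 0.10 SD | 8.4% |
| 20% / 10% | 1 SD, intervention only | 0.20 SD | 18.9% |

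The first row matters as much as the last: with equal loss, equally related to outcome, there is no bias.

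**The case against.** The strongest reply is that the document cannot show that the completers rule does bias the result. That stands. Completers-only is unbiased if data are missing completely at random, or if loss and its link to outcome are the same in both arms. The 10-point gap, the SDs and the one-sided loss are all assumed. The document supports only that the rule can bias the comparison. Neither protective condition is assured, however: patients may stop at any time, the arms differ in content, and only assessors are described as blinded.

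A second reply is that the missingness test and expectation maximization show an intention to use incomplete cases. That is fair and should be acknowledged, but it sharpens the conflict with the completers sentence rather than resolving it.

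Some stronger readings are tempting but unsupported:

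- **A power shortfall.** If each of the three visits were independently missed by 10%, only 0.9^3 = 72.9% would complete all of them, and power would be about 0.74. That is 27% loss against a planned 15%, and it uses an effect size back-solved from the stated total. If each visit were missed by 5%, 1 - 0.95^3 = 14.3% would be incomplete, within the allowance. The document shows no departure from its stated power of 0.80.
- **A heavier intervention programme that drives dropout.** The Interventions section gives both arms the same number and length of sessions and daily home exercise.
- **Removal of harmed patients by rule.** The sentence on serious adverse events in the withdrawal section is garbled. It probably permits stopping, but it does not say that such patients leave follow-up or the analysis.
- **Telephone collection of both primary outcomes.** The reliability cited under Primary outcomes is for the ODI only.

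**Conclusion.** The point stands and should be fixed. The Data analysis section gives two incompatible rules for who is analysed, with no order of precedence, and the withdrawal section leans towards the weaker one. Followed as written, the completers rule removes about 20 of 136 randomised patients at the planned 15% dropout, plus any with a valid 12-week ODI who missed an earlier visit and are not already counted in that allowance.

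The statistical harm is conditional. Type I error stays at 5.0% if loss is balanced and equally related to outcome. It rises to about 7% to 10% in the ODI scenario above, and further under more extreme assumptions. The size and direction in this trial cannot be derived from the document. The 15% inflation of the sample protects precision; it does not restore the randomised comparison. The contradiction itself depends on none of these assumptions.

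**What to change.** 1. Delete the completers-only sentence in the Data analysis section and the matching sentence in the Withdrawal and drop-out criteria section.
2. Remove the restriction of intention-to-treat to dropouts with unavoidable reasons.
3. State that the primary analysis includes every randomised participant in the allocated arm, using all observed visits in a method valid under missing at random. A likelihood-based repeated-measures model or multiple imputation would serve. Name the method, because a classical repeated-measures analysis of variance that drops incomplete records would bring the completers rule back.
4. Report the completers analysis as a sensitivity analysis, labelled as such.
5. Continue outcome collection after treatment is stopped, where the participant has not withdrawn from the study.

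These methods remove bias only so far as the observed data explain the loss, so the error rates above do not measure what the change would gain.

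The cost is protocol wording and slightly more analysis work; no extra patients are needed. The Trial status section says recruitment is under way, so the change should be made and dated before outcome data are examined by arm.
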